#### Sample size

2.2.1

In this study, the sample size was calculated according to following repeated measurement formula: 

Where N is the sample size of each groups, α is the significance level (0.05), β is related to study power (0.2) σ^2^ is the variance of measurements, δ is minimum effect size, *p* is the number of observations before treatment of each participant, *r* is the number of observations after treatment of each participant and ρ = 0.65. Based on our previous pilot study^[30]^ with the standard deviation of VAS-P values of 19.67 after 30 minute treatment and minimum clinical effective changes of VAS-P of 10 mm, we calculated that a sample size of 20 per group was a necessary to provide 80% power to detect a difference in the VAS-P value between two groups, considering a 20% drop-out rate, 24 participants are required per group.

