### Interventions

2.5

Acupuncture treatment will be implemented, when the participants VAS-P score of menstrual pain in the first day of menstruation is equal to or more than 40 mm. Both groups will be received an acupuncture treatment for 10 minutes at bilateral SP6 acupuncture points, after sterilizing the skin on the areas where the needles will be inserted, by using single-use sterile filiform needles of 0.30 × 40 mm (Zhongyan Taihe, Beijing Zhongyan Taihe Medical Instruments center, Beijing, China). In perpendicular needling group, the needles will be vertically inserted to SP6 bilaterally in a depth of 1 to 1.2 cun and will be manipulated by lifting-thrusting and twirling methods for 30 seconds to achieve proper needling sensation. In transverse needling group, the needles will be inserted to bilateral SP6 transversely 1 to 1.2 cun toward the abdomen without any manipulation to avoid needling sensation. The location of the acupoint and 2 needling techniques are shown in Figure 2.

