### Statistical analysis

2.8

All statistical analyses will be performed using SPSS 20.0 software (IBM, Armonk, NY) by statistician, who is independent from the research team and blinded to patient allocation. The effects of different needling technique on PD will be analyzed on an intention-to-treat (ITT) approach. To evaluate the sensitivity of analysis, the results of the ITT analysis will be compared with those of per-protocol analysis. Baseline demographic and clinical characteristics of participants will be reported as mean (standard deviation) for continuous variables, and as frequencies (percentages) for categorical variables. Repeated measures analysis of variance (ANOVA) will be used for the analysis of variables, which will be measured at several different times. For other variables, 1-way ANOVA or non-parametric Mann-Whitney *U* test will be applied. Mean differences from baseline to post-treatment in each group will be assessed using paired *t* tests or Wilcoxon signed rank tests. *P* < .05 will be considered significant.

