In current study, sham acupuncture group is not set. The main reason is that the main purpose of this study is to compare the effective of 2 needling techniques at SP6 for PD, so it is a noninferiority trail.^[46]^ Moreover, those 2 treatment methods have been proven effective in previous studies. For example, perpendicular needling at SP6 showed more effective results for PD compared with other acupoint, nonacupoint and waiting list controls in a series studies of our research group,^[19,22,23]^ particularly in cold-damp stagnation TCM pattern^[26]^ and compared with nondeqi needing (similar to the intervention of sham acupuncture in the majority of studies).^[27]^ Superficial transverse needling at the location of SP6 on PD patients also showed better pain-relief effect than analgesia medication.^[29,47]^ A latest review^[48]^ pointed that placebo might not be as distinctively defined as it is necessary for conducting a clinical trial in the non-pharmacological arena, such as acupuncture, and pragmatic approach should aim to maximize all the positive factors of a treatment that can be recruited while minimizing risk and negative effects.

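### Section 2.8 plans within-arm paired tests at P < .05 without calling them descriptive; with two active arms they can neither attribute a fall in pain to needling nor compare the techniques

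*Protocol article*

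**What the plan says.** Section 2.8 (Statistical analysis) lists three kinds of test. Outcomes measured at several times go to repeated measures ANOVA. Other variables go to one-way ANOVA or the Mann-Whitney test. Then: "Mean differences from baseline to post-treatment in each group will be assessed using paired" t tests or Wilcoxon signed rank tests. One threshold, P < .05, closes the section and applies to all three. Nothing marks the paired tests as descriptive or supplementary.

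The setting for those tests is fixed elsewhere in the article:

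- **Entry.** Section 2.5 gives treatment only when the "VAS-P score of menstrual pain in the first day of menstruation is equal to or more than 40 mm".
- **Control.** Section 3.1: "In current study, sham acupuncture group is not set". Both arms receive needling at SP6.
- **Rescue.** Section 2.5 allows aspirin above 80 mm.
- **Aim and size.** The Introduction compares transverse with perpendicular needling. Section 2.2.1 sizes the trial for "80% power to detect a difference in the VAS-P value between two groups".

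**The concern.** A paired test within one arm asks whether the mean changed from baseline. It does not ask why. Women enter at a moment when pain is at or above a threshold, and the last VAS-P is 40 minutes after needling starts (10 minutes of needling plus 30 minutes after removal). Pain may fall over that time without any effect of needling, and no arm shows by how much.

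The second risk is the comparison of two P values. The Introduction recalls that perpendicular needling showed no effect on uterine flow in an earlier study and hypothesises that transverse needling improves flow better. A significant paired test in the transverse arm and a non-significant one in the perpendicular arm would look like confirmation. That pattern arises often when the two arms change by the same amount.

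**Working it through.** **Inputs.** From section 2.2.1: "standard deviation of VAS-P values of 19.67 after 30 minute treatment", ρ = 0.65, "minimum clinical effective changes of VAS-P of 10 mm", α = 0.05 (taken as two-sided; the article does not say), power 80%, and 20 per group raised to 24 for drop-out. From section 2.6.1: one VAS-P before and four after needling (p = 1, r = 4).

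**1. What the plan's sample size rests on.** The formula itself is not legible in the text at hand, so three standard repeated-measures forms were tried. All share the factor 2(1.960 + 0.842)² × 19.67² / 10² = 60.74.

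| Form | Multiplier | n per group |
|---|---|---|
| Baseline-adjusted | (1 + 3 × 0.65)/4 − 0.65² = 0.7375 − 0.4225 = 0.315 | 19.1, rounded up to 20 |
| Change score | 0.7375 − 2 × 0.65 + 1 = 0.4375 | 26.6 |
| Post-treatment mean only | 0.7375 | 44.8 |

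Only the baseline-adjusted between-group form gives the stated 20.

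**2. Same true change in both arms.** SD of a paired change = 19.67 × √(2 × 0.35) = 16.46 mm. With 24 per arm, SE = 16.46/√24 = 3.36 mm. Let π be the power of one arm's paired t test (23 df, critical value 2.07). The arms are independent, so exactly one is significant with probability 2π(1 − π).

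| True change in each arm (mm) | Power per arm | Exactly one arm significant |
|---|---|---|
| 5 | 0.30 | 42% |
| 6.5 | 0.46 | 50% |
| 8 | 0.63 | 47% |
| 10 | 0.81 | 30% |
| 12 | 0.93 | 13% |
| 15 | 0.99 | 2% |

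With 20 per arm and a 10 mm change the figures are 0.73 and 39%. The article gives no expected within-arm change, so the left column is assumed. The same logic holds for PI, RI and S/D, but the article gives no SDs from which to work out a size.

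**3. Regression to the mean in VAS-P.** Assume normal scores with SD 19.67, that the qualifying score is also the baseline, and no effect of needling. For unselected mean μ, let a = (40 − μ)/19.67. The expected fall is (1 − 0.65) × 19.67 × φ(a)/(1 − Φ(a)). The article does not give μ, so a range is shown.

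| Assumed μ (mm) | Expected fall (mm) | Chance of a significant fall, 24 per arm |
|---|---|---|
| 40 | 5.5 | 38% |
| 50 | 3.5 | 18% |
| 55 | 2.6 | 12% |
| 60 | 1.9 | 8% |
| 70 | 0.9 | 4.5% |

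The nominal chance in that direction is 2.5%. Natural course, expectation and aspirin come on top and cannot be sized from the article.

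**4. Does the between-group test share the fault?** In 4,000 simulated trials with μ = 55, 20 per arm and no effect of needling, the group-by-time test of the ANOVA was significant in 5.8%, close to nominal. The paired test was significant in 10.7% of arms, exactly one arm was significant in 18.9% of trials, and the ANOVA time effect was significant in 14.3%.

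**The case against.** The strongest reply is that the plan does not depend on these tests. Section 2.8 names repeated measures ANOVA first; it covers VAS-P, the Doppler indices, blood pressure and heart rate. The remaining outcomes get tests that compare the two arms. The aim and the sample size are between-group. A reader might infer that the paired tests are the plan's only basis for judging analgesia. The documents do not support that: every outcome has a planned test able to compare the arms. Nor does any sentence say that discordant paired tests will be read as a difference. Both parts of this reply stand.

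The lack of a sham arm is explained in section 3.1 and listed in section 3.5, so it is not hidden. That also stands. But section 3.5 describes the consequence as reduced power, whereas the difficulty is attribution, which more patients would not cure. Disclosure also does not make a within-arm P value informative about needling.

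The size depends on assumptions. Discordance is large only for true changes around or below the plan's own 10 mm minimum, and it nearly vanishes at 15 mm. Regression to the mean is small if typical pain is well above 40 mm. It has been shown for VAS-P only, because selection is on pain and not on Doppler indices. All of this is accepted.

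Finally, ranking of tests is often left to an analysis plan. Here, however, the article itself fixes the paired tests and attaches the significance threshold to them.

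**Conclusion.** The point holds in a limited form. The within-arm paired tests are a weak supplementary element beside a sound between-group analysis, but they are stated as inferential. They cannot attribute a fall in VAS-P to either technique. Any statement about one technique's own effect rests on change from baseline alone, whether by paired test or by the ANOVA time effect.

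Nor can they compare techniques. Identical arms disagree in about 30% to 50% of trials if the true change is 5 to 10 mm, and in 13% and 2% at 12 and 15 mm. Regression to the mean contributes about 1 to 5 mm of apparent VAS-P relief. These figures rest on the plan's SD and correlation, 24 per arm, assumed true changes and an assumed unselected mean of 40 to 70 mm. The correction is worth making because it costs little and agrees with how the trial was sized.

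**What to change.** In section 2.8, replace the paired-test sentence with two statements:

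1. Within-arm changes from baseline are reported as means with 95% CIs, without P values.
2. Conclusions on analgesia and on uterine blood flow rest on the between-group difference, adjusted for the baseline value already collected, with its 95% CI.

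This needs no extra patients, visits or measurements. The within-arm P values are lost, and the model changes slightly, since the comparison is now stated as a baseline-adjusted difference where section 2.8 names only repeated measures ANOVA. That change brings the analysis into line with the only form of the sample size formula tried that gives 20 per group.

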## Discussion

3

This study is designed to illustrate the influence of needling techniques on the therapeutic result of the acupoint. It will perform perpendicular or transverse needling with same length of needle body embedded in a solo acupoint and compare analgesia and hemodynamic responses right after needling.

### Needling technique is essential for efficacy of acupoints

3.1

The use of specific needling techniques for treatment of different type of pathology can be traced back to Huangdi Neijing.^[39]^ Various needling techniques such as subcutaneous needling, triple-directional needling, waggle needling, and short needling recorded in Neijing are usually used for relevant disorders of skin, muscle, sinew, and bone, respectively. With gradual development in each generation, the perception of applying needling technique which should be suitable for the disease is now widely accepted by modern acupuncturists.

Needling technique, is considered as one of the most significant factors in the curative efficacy of acupoints, which related to depth, intensity and duration.^[40]^ There is both theoretical and empirical support for the hypothesis that alterations in needling technique have an impact on therapeutic outcomes. Sun et al in their systematic review, found relation between needling depth and therapeutic efficacy in lumbar disk herniation.^[41]^ Studies reported that the different depths which were used in acupuncture needling can lead to different impression on the central nervous system and different clinical therapeutic effects.^[42,43]^

According to the clinical experience of acupuncture practice, needling depth and angle of insertion are always considered in combination. Thus, some innovative needling methods such as ankle-wrist acupuncture^[44]^ and Fu's subcutaneous needling^[45]^ are developed, with advantages of no or less needling sensation. As a classic acupoint for PD, the needling techniques at SP6 in the previous studies focused only on needling depths,^[27]^ or only compare transverse needling with medications.^[29]^ At present, there are few attentions paid to the influence of comprehensive factors of needling including depth and angle, on the efficacy of same acupoint. Therefore, the efficacy of transverse subcutaneous needling at SP6 for PD should be investigated further in clinical trials. In addition, because it lacks a clear scientific explanation, the underlying mechanism deserves further study.

In current study, sham acupuncture group is not set. The main reason is that the main purpose of this study is to compare the effective of 2 needling techniques at SP6 for PD, so it is a noninferiority trail.^[46]^ Moreover, those 2 treatment methods have been proven effective in previous studies. For example, perpendicular needling at SP6 showed more effective results for PD compared with other acupoint, nonacupoint and waiting list controls in a series studies of our research group,^[19,22,23]^ particularly in cold-damp stagnation TCM pattern^[26]^ and compared with nondeqi needing (similar to the intervention of sham acupuncture in the majority of studies).^[27]^ Superficial transverse needling at the location of SP6 on PD patients also showed better pain-relief effect than analgesia medication.^[29,47]^ A latest review^[48]^ pointed that placebo might not be as distinctively defined as it is necessary for conducting a clinical trial in the non-pharmacological arena, such as acupuncture, and pragmatic approach should aim to maximize all the positive factors of a treatment that can be recruited while minimizing risk and negative effects.

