According to classic Chinese acupuncture theory, applying proper needling technique, particularly the depth, angle, and direction of the needling at an acupoint, is an essential point which may contribute to the results of acupuncture. Our previous study showed that perpendicular deep needling at SP6 to induce strong needling sensation had better pain-relief effect for PD patients compared to perpendicular superficial needling.^[27]^ However, many patients particularly in western countries did not like needling sensation, and their attitude might affect the manipulation of the acupuncturists.^[28]^ Transverse needling has advantage of less pain, and easy to be accepted in large number of patients who are afraid of needling sensation. One study showed that transverse superficial needling at SP6 on PD is better than that of oral administration of indomethacin enteric-coated tablets.^[29]^ We also found^[30]^ that transverse superficial needling at SP6 had similar significant immediate analgesic effect in PD patients as perpendicular deep needling. However, the underlying mechanism of pain-relief effect of transverse needling remains unclear and worthy of further study.

Studies showed that the menstrual pain is closely related to the decreased uterine blood flow,^[31]^ and a high resistance against blood flow in the uterus was found in doppler indices.^[32]^ Our previous study showed that although perpendicular needling at SP6 could immediately relive menstrual pain, it did not show the effects on uterine arterial blood flow in PD patients.^[23]^ Another animal study revealed that transverse needling had analgesia effect through decreasing prostaglandin (PG) F2α, increasing β-endorphin, nitric oxide, and substance P to relieve uterine cramps, increase blood flow.^[33]^ Therefore, we hypothesized that compared with perpendicular needling, the analgesia effect of transverse needling at SP6 may be achieved by better improving uterine arterial blood flow.

This study is designed to investigate the immediate analgesic effect and uterine arterial blood flow changes of transverse needling at SP6 versus perpendicular needling for treatment of PD.

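### The article labels the study a noninferiority trial but sizes and tests it only for a difference, so the written analysis cannot support a noninferiority conclusion

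*Protocol article*

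**What the plan says.** The design label appears once in the Protocol article, in section 3.1, where the absence of a sham arm is explained. The main purpose is said to be to "compare the effective of 2 needling techniques at SP6 for PD, so it is a noninferiority trail".

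The sections that set the size and the analysis describe something else:

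- Section 2.2.1 (Sample size) aims at "80% power to detect a difference in the VAS-P value between two groups". Its δ is a minimum effect size, given as "minimum clinical effective changes of VAS-P of 10 mm", and is not called a margin.
- Section 2.8 (Statistical analysis) names repeated measures ANOVA for outcomes measured several times, one-way ANOVA or Mann-Whitney tests for the others, and paired tests within groups. The only decision rule is that a P value "< .05 will be considered significant". Intention-to-treat is the main approach, and per-protocol is a sensitivity comparison.

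Neither section says which technique is the reference, and neither compares a confidence limit with a margin.

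**The concern.** A noninferiority claim needs a margin fixed in advance and a confidence limit that excludes it. A test of no difference does not supply this: failing to reject equality is not evidence that the deficit is small. The label in 3.1 and the rule in 2.8 therefore do not fit together. The label carries weight, because it is the stated reason for a design decision.

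The Introduction makes the issue practical. It reports that an earlier study by the same group, the one that also supplies the SD for the sample size, found a similar immediate analgesic effect with the two techniques. A non-significant pain comparison is thus a realistic result. With a noninferiority label and only a P < .05 rule, a reader could take that result as showing that one technique is no worse than the other, with no control over the error of that claim.

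**Working it through.** **Inputs**

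- From 2.2.1: "standard deviation of VAS-P values of 19.67 after 30 minute treatment" (SD 19.67 mm), δ = 10 mm, ρ = 0.65, α = 0.05, power 80%, 20 per group before dropout and 24 after.
- From the VAS-P schedule in 2.6.1: one reading before needling and four after, so p = 1 and r = 4. The article gives no numbers for p and r, and the formula image is not shown. These values and two-sided testing are inferred.

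**1. Reproduce the stated size**

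Baseline-adjusted repeated-measures formula: N = 2(z₀.₉₇₅ + z₀.₈)² × SD²/δ² × F, with F = [1 + (r − 1)ρ]/r − pρ²/[1 + (p − 1)ρ].

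- F = (1 + 3 × 0.65)/4 − 0.65² = 0.7375 − 0.4225 = 0.315.
- 2 × 7.849 × 19.67²/100 = 60.74.
- N = 60.74 × 0.315 = 19.13, rounded up to 20.
- 20 × 1.2 = 24.

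The stated figures follow as a two-sided 5% calculation for a difference. A one-sided 5% test would give 15.07, so 16.

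**2. Precision with 20 evaluable per group**

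- SE = √(2 × 0.315 × 19.67²/20) = 3.49 mm.
- 95% half-width = 1.96 × 3.49 = 6.8 mm (6.2 mm with 24 per group).

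**3. How often a real deficit gives P > .05**

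- True 10 mm: 10/3.49 − 1.96 = 0.90, power 81.7%, so 18% non-significant. A t reference distribution makes this about 20%, which is the plan's own β. With 24 per group the normal figure is 12%.
- True 5 mm: 5/3.49 − 1.96 = −0.53, power 29.9%, so 70% non-significant (65% with 24 per group).

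If noninferiority is concluded only when the 95% confidence limit lies inside the margin, a true deficit equal to the margin passes 2.5% of the time. The fair comparisons are therefore 18–20% against 2.5% for a 10 mm margin, and 70% against 2.5% for a 5 mm margin.

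**4. Size if noninferiority were intended**

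The article gives no margin, so a range is assumed: one-sided 0.025, 80% power, true difference 0, F = 0.315. Then N = 2 × 7.849 × 19.67² × 0.315/margin² = 1913/margin².

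| Margin | N per group, evaluable |
|---|---|
| 10 mm | 19.1, so 20 |
| 8 mm | 29.9, so 30 |
| 5 mm | 76.5, so 77 |

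Without baseline adjustment, using the mean of the four later readings (F = 0.7375), a 10 mm margin needs 60.74 × 0.7375 = 44.8, so 45.

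**The case against.** The best defence is that the operative plan is coherent. The word occurs once, in the Discussion. The abstract and section 2 never use it, and the sample size reproduces as a difference calculation. On this view there is a stray label and nothing more. Much of that stands: primary outcome, arms, planned test and stated N do not depend on the label. It does not remove the contradiction, because the label justifies the absence of a sham arm. An unseen analysis plan could add a margin, but it could not reconcile 3.1 with the sizing aim and decision rule that the article already fixes.

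Several stronger readings are tempting, and the article does not support them:

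- **That P > .05 will be reported as noninferiority.** No section says so. It is a risk left open by the label.
- **That the Introduction's hypothesis contradicts noninferiority on pain.** It says that "compared with perpendicular needling, the analgesia effect of transverse needling at SP6 may be achieved by better improving uterine arterial blood flow". This concerns blood flow, a secondary outcome, and can coexist with a noninferiority aim for pain. No formal VAS-P hypothesis is stated.
- **That the transverse arm is in effect a sham.** The needling that 3.1 likens to sham is cited to a study which the Introduction describes as using perpendicular superficial needling. The missing sham arm is already listed in 3.5, and removing the label would not change that limitation.
- **That the false-claim rate is 55–69%.** Those figures arise if the group effect of the repeated measures ANOVA is taken without baseline adjustment. That is a separate mismatch between the sizing formula and the named analysis.
- **That a noninferiority conclusion would be false.** If the techniques are truly similar, it would be unproven rather than wrong. The rates in the working are conditional on a real deficit.

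**Conclusion.** The point holds as an internal contradiction between 3.1 on one side and 2.2.1 and 2.8 on the other. The analysis as written can show a difference but cannot show noninferiority. Reading non-significance as noninferiority would pass a true 10 mm deficit about 18–20% of the time and a true 5 mm deficit about 70%, against 2.5% for a valid test whose margin equals the deficit. These figures assume SD 19.67, ρ = 0.65, one baseline and four later readings, baseline adjustment and 20 evaluable per group.

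The sample size is not wrong for a difference trial. It coincides with a noninferiority size for a 10 mm margin and zero true difference, from which a reader might infer that 10 mm is the margin. The article does not call it one, and using it would mean accepting a deficit as large as the plan's whole minimum clinically effective change.

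**What to change.** **Preferred.** In 3.1, delete the closing clause that calls the study a noninferiority trial. In 2.2.1 and 2.8, describe a two-sided comparison of the techniques. Add to 2.8 that the between-group VAS-P difference will be reported with its 95% confidence interval, and that a non-significant result will not be interpreted as noninferiority or equivalence. The cost is a few sentences, with no change to size, arms or outcome.

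**If noninferiority is truly intended.** Name the test and reference techniques. Prespecify and justify a margin. Use a baseline-adjusted analysis and compare the upper 95% confidence limit for the deficit (test minus reference, higher VAS-P being worse) with that margin. Require intention-to-treat and per-protocol to agree, rather than treating the second as a sensitivity check. This is more than wording, because it changes the primary analysis. The present 20 per group is enough only for a 10 mm margin with zero true difference and baseline adjustment. A margin of 8 mm needs about 30 per group and 5 mm about 77, before dropout.
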